## Abstract

**Background:**

Patients with incurable gastroesophageal adenocarcinoma have an impaired health-related quality of life (HRQOL). Exercise combined with nutritional support may improve this outcome. Careful evaluation of this supportive care strategy is needed to avoid burdening patients at this vulnerable stage with interventions that may offer no (meaningful) benefit. Therefore, this study aims to investigate the effects of a combined exercise and nutritional intervention on HRQOL in patients with incurable gastroesophageal adenocarcinoma.

**Methods:**

RADICES (the effect of exeRcise And Diet on quality of life in patients with Incurable Cancer of Esophagus and Stomach) is a multicenter randomized controlled trial aiming to include 196 patients with incurable gastroesophageal adenocarcinoma. Participants are randomly assigned (1:1) to a patient-tailored intervention or a control group. The intervention group is provided with 2 training sessions per week and biweekly nutritional consultations, delivered by trained physiotherapists and dietitians, during 12 weeks. The control group receives usual care supplemented with general physical activity advice. The primary outcome is the difference in HRQOL between the intervention group and the control group at 12 weeks, accounting for baseline HRQOL, measured by the European Organization for Research and Treatment of Cancer Quality of Life Questionnaire–30 summary score. HRQOL is assessed at baseline, 6 weeks, 12 weeks, and every 3 months thereafter up to 1 year. Key secondary outcomes include patient-reported outcomes, cardiorespiratory fitness, dietary intake, disease progression, overall survival, and cost-effectiveness. Adherence and safety are monitored throughout the intervention period.

**Conclusion:**

This study will generate evidence on the effectiveness of a patient-tailored combined exercise and nutritional intervention in patients with incurable gastroesophageal adenocarcinoma. If effective for HRQOL, this intervention could be integrated into standard care for patients with incurable gastroesophageal adenocarcinoma.

**Trial registration:**

clinicaltrials.gov NCT06138223.

**Date of trial registration:** November 18, 2023

**Date and version study protocol:** 28-04-2025 version 3.1

**Date start recruitment:** 19-01-2024

## Introduction

For approximately 70% of patients diagnosed with gastroesophageal (adeno)carcinoma, curative treatment is not possible because of advanced disease and/or comorbidities.^1^ The survival of patients with incurable gastroesophageal adenocarcinoma is poor. For patients receiving best supportive care, survival is typically limited to a few months, whereas palliative systemic treatment can extend median survival to more than a year.^2-4^ In patients with incurable gastroesophageal adenocarcinoma, regardless of palliative treatment, health-related quality of life (HRQOL) is impaired.^5^^,^^6^ Across various cancer populations, potentially reversible factors contributing to this include reduced muscle mass, reduced physical capacity, and poor nutritional status.^7-9^

Exercise has been shown to positively affect multiple outcomes, including HRQOL and disease-free survival, during and after curative cancer treatment.^10-16^ In the metastatic breast cancer setting, a recent trial demonstrated beneficial exercise effects on HRQOL.^17^ Additionally, 2 systematic reviews support the safety and feasibility of exercise interventions in patients with different types of advanced cancer.^18^^,^^19^ However, specific evidence in patients with incurable gastroesophageal adenocarcinoma is lacking.^20^

Patients with incurable gastroesophageal adenocarcinoma are often malnourished,^21-24^ with reported prevalence rates between 80% and 96% in advanced stages of the disease, due to a combination of reduced appetite, impaired digestion and absorption, and metabolic changes.^25-29^ Moreover, the majority of these patients have a suboptimal energy and protein intake,^30-32^ although appropriate nutrition is essential for optimal exercise effects,^33^ and improvement of nutritional status has even been associated with increased survival.^34-36^

Although studies combining exercise and nutrition have been conducted, they mainly consist of pilot studies, take place in the curative setting, or consist of a population with different advanced cancer types.^14^^,^^37-41^ Two trials reported that a combined exercise and nutritional intervention is feasible (ie, attendance above 75%) and safe in patients with advanced cancer, including patients with incurable gastroesophageal adenocarcinoma.^37^^,^^38^ Also, improvements in handgrip strength,^38^ protein intake, and nausea and vomiting^37^ were observed in the exercise groups, but no effects on HRQOL could be detected, probably because of small sample sizes. More research is needed in incurable gastroesophageal adenocarcinoma patients to evaluate such a combined personalized intervention carefully,^20^ to avoid burdening patients at this vulnerable stage with interventions that may offer no meaningful benefit, and to ensure safety.

The RADICES (Effect of Exercise And Diet on Quality of Life in Patients with Incurable Cancer of Esophagus and Stomach) study has been primarily designed to investigate the effect of a 12-week combined exercise and nutritional intervention on HRQOL in patients with incurable gastroesophageal adenocarcinoma. Second, this study investigates, among others, the effects on other patient-reported outcomes, cardiorespiratory fitness, dietary intake, disease progression, overall survival, and cost-effectiveness. This article describes the design of the RADICES study.

## Methods

### Design

The RADICES study is a multicenter, randomized controlled trial with 2 study arms: (1) the intervention arm, which follows a 12-week patient-tailored combined supervised exercise and nutritional intervention in addition to usual care; and (2) the control arm, which receives a general physical activity and nutritional advice in addition to usual care. Both groups receive an activity tracker. The RADICES study protocol has been approved by the medical ethics committee of the Amsterdam University Medical Center (2023.0310—NL83835.018.23) in September 2023. Written informed consent will be obtained from all participants. The study is registered at clinicaltrials.gov under NCT06138223.^42^ The first patient was included on January 19, 2024. This study is being conducted according to the guidelines laid down in the Declaration of Helsinki.

### Participants

In the RADICES study, we aim to include 196 patients. To be eligible, patients need to meet the following inclusion criteria: incurable adenocarcinoma of esophagus or stomach with recurrence after treatment with curative intent or irresectable or metastatic disease at primary diagnosis, aged 18 years and older, able and willing to perform the exercise and nutritional intervention and wear an activity tracker, able and willing to fill out the questionnaires, and a life expectancy of at least 12 weeks as determined by the treating physician. Exclusion criteria are presence of unstable bone metastases inducing skeletal fragility, untreated symptomatic brain metastasis, serious active infection, being too physically active (ie, >210 min/week of moderate-to-vigorous exercise) or already engaging in an exercise program comparable to the RADICES exercise intervention, severe neurologic or cardiac impairment according to the American College of Sports Medicine criteria,^43^ uncontrolled severe respiratory insufficiency or being dependent on oxygen supplementation in rest or during exercise, uncontrolled severe pain, any other contraindications for exercise, pregnancy, and any (other) circumstances that would impede adherence to study requirements or ability to give informed consent. Medical inclusion and exclusion criteria are checked by the treating physician.

### Recruitment and random assignment

Participants are being recruited from 22 hospitals across the Netherlands (Figure 1). Potentially eligible patients are informed about the study by the oncology nurse or medical specialist. Interested patients receive a patient information letter explaining the study aims and procedures. Subsequently, the patients are approached by the research team via telephone to provide further information, answer remaining questions, and verify inclusion and exclusion criteria. Patients who choose not to participate in the RADICES study are asked, but not required, to provide their reason for nonparticipation.

**Figure 1. pkag006-F1:**
[figure not shown]
Recruitment and study procedures. Abbreviations: p.w. = per week; RADICES = effect of exeRcise And Diet on quality of life in patients with Incurable Cancer of Esophagus and Stomach.

Eligible patients who are willing to participate are invited to the hospital to provide written informed consent and undergo baseline measurements. Hereafter, participants are randomly allocated (1:1) to either the combined exercise and nutritional intervention or the control group. All participants receive usual care according to the guidelines of their treating hospital, which generally includes systemic anticancer treatment and may include nutritional care if indicated. If hospitals refer patients to a physiotherapist who prescribes an exercise program comparable to the RADICES exercise intervention, these patients are not eligible for participation in our study. For the allocation procedure, a blocked computer-generated sequence (Castor EDC) is used, effectively blinding random assignment. Random assignment is stratified by the World Health Organization (WHO) performance status (0 vs 1 and higher) and treatment line (first vs second line or higher or best supportive care). Because of the nature of the intervention, participants, local medical staff, and investigators are not blinded to treatment assignment.

### Combined exercise and nutritional intervention

#### Exercise intervention

The exercise intervention consists of a moderate-to-high intensity 12-week supervised combined aerobic and resistance exercise program, with sessions lasting 1 hour, twice a week. The program is supervised by a trained (oncology) physiotherapist and is offered at a physical therapy practice located near the participants’ home address. Each participant has an intake session to tailor the standard exercise prescription to their individual needs. During the intervention, exercise intensity will be progressively increased and individually adjusted according to the participant’s current health status and perceived exertion, which are systematically assessed before, during, and after each exercise session. For a detailed description of the exercise program, see Supplementary Methods 1.

#### Nutritional intervention

The nutritional intervention consists of biweekly 30-minute consultations with a dedicated oncology dietitian. These consultations are held on-site or, if preferred by the participant, via telephone or video call. The dietitian will perform a nutritional assessment, make a dietetic diagnosis, set personalized nutritional goals, and provide individualized nutritional advice, taking into account treatment-related side effects (eg, nausea, taste changes), food preferences, and any alterations to the esophagus and stomach anatomy due to surgery.^28^ The purpose of the nutritional part of the intervention is to improve or maintain nutritional status by (1) preserving body weight (improvement of body weight when body mass index is less than 18.5 kg/m^2^ or when less than 20 kg/m^2^ if older than 65 years), (2) preserving or improving muscle mass and muscle strength, and (3) striving for sufficient energy and protein intake. Goals for energy and protein intake will be adjusted on an individual basis guided by monitoring body weight. The European Society for Clinical Nutrition and Metabolism guideline and the national guidelines of the National Nutritionists Oncology Working Group provide the means to reach this purpose.^44^^,^^45^ Additional details of the nutritional intervention are provided in Supplementary Methods 2.

### Control group

Participants in the control group receive usual care supplemented with general physical activity and nutritional advice according to current guidelines.^10^^,^^44^^,^^46^ During the 12-week intervention period, they are asked to maintain their usual physical activity pattern (ie, to not consult a physiotherapist if they had not done so before inclusion) and to avoid inactivity.

### Study outcomes

Participants visit the participating hospital for questionnaires and physical measurements at baseline and 12 weeks postbaseline (Table 1).

**Table 1. pkag006-T1:** Overview of all measurements in the RADICES study

Outcomes	Instrument	T0	T1	T2	Follow-up
		Baseline	6 weeks	12 weeks	Every 12 weeks
Primary outcome					
Health-related quality of life — summary score	EORTC QLQ-C30^47^	X	X	X	X
Secondary outcomes					
Patient-reported outcomes					
Quality of life functional and symptom scales	EORTC QLQ-C30^47^	X	X	X	X
Physical functioning, role functioning, fatigue	Computer adaptive testing	Every 2 weeks during intervention period			
Esophagogastric cancer specific symptoms	EORTC-QLQ-OG25^48^	X		X	X
Anxiety and depression	Hospital Anxiety and Depression Scale^49^	X		X	X
Physical measurements					
Resting heart rate and blood pressure	Blood pressure monitor	X		X	
Physical fitness	Steep Ramp Test, handgrip- and leg-strength test	X		X	
Anthropometry	Weighting scale (InBody Dial H20B)^50^	X		X	
Body mass index					
Body composition	Weighting scale (InBody Dial H20B)^50^, computed tomography scan	X		X	
Physical activity					
Self-reported (subjective)	Short questionnaire to assess health enhancing physical activity ^51^	X		X	X
Objectively measured physical activity	Physical activity tracker (Fitbit Inspire 2)	X		X	
Nutritional outcomes					
Malnutrition risk	Abridged Patient-Generated Subjective Global Assessment Short Form^52^	X		X	X
Sarcopenia risk	SARC-F^53^	X		X	X
Nutritional intake	Nutritional diary	X		X	
Cost-effectiveness					
QALY	EQ-5D-5L^54^	X		X	X
Productivity loss	Productivity Cost Questionnaire (IPCQ)^55^	X		X	X
Health-care resources consumption	Medical Consumption Questionnaire (iMCQ)^56^	X		X	X
Socio-demographic and medical data					
Sociodemographic data	POCOP questionnaire	X		X	X
World Health Organization performance status	Medical records	X		X	
Medical history and concomitant diseases	Medical records	X			
Cancer progress and treatment over the course of the study	Medical records	X		X	X
Cancer characteristics and treatment history	Medical records	X			
Concomitant medication	Medical records, interview	X		X	
Adverse events	Reports of patients, trainers, dietitians, oncology nurses, physicians, or medical records	X		X	
Toxicity and systemic treatment-related adverse events	Medical records	X	X	X	X
Overall survival and progression-free survival	Medical records and/or cancer registry	X	X	X	X
Intervention-specific outcomes					
Satisfaction with the intervention	Self-developed questionnaire			X	
Adherence	Recording session/consultation attendance			X	
Safety	Recording intervention-related (serious) adverse event	During the whole intervention period			

Abbreviations: EORTC-QLQ-C30 = European Organization for Research and Treatment of Cancer Quality of Life Questionnaire; EQ-5D-5L = EuroQol 5-Dimension 5-Level; iMCQ = iMTA Medical Cost Questionnaire; IPCQ = iMTA Productivity Cost Questionnaire; POCOP = Prospective Observational Cohort Study of Oesophageal-gastric Cancer Patients; RADICES = Effects of Exercise and Diet on Quality of Life in Patients with Incurable Cancer of Esophagus and Stomach; SARC-F = Strength, Ambulation, Rising from a Chair, Stair Climbing and History of Falling; SQUASH = Short questionnaire to assess health enhancing physical activity.

For those undergoing chemotherapy, assessments take place at least 3 days after chemotherapy infusion. Questionnaires are completed online or on paper at baseline, 6 weeks, and 12 weeks postbaseline. Additionally, every 2 weeks, patients receive a link via email to fill out computer adaptive testing questions. Subsequently, questionnaires are sent every 12 weeks up to 1 year postintervention. Questionnaires are sent through the Prospective Observational Cohort study of Oesophageal-gastric cancer Patients (POCOP) study, which is a prospective observational study for all Dutch patients with gastroesophageal cancer.^57^ After 1 year, participants will continue to be followed according to the POCOP study protocol. Furthermore, participants fill out a 3-day nutritional diary at baseline and at 12 weeks postbaseline. Personal data are coded, and all data are handled according to the General Data Protection Regulation (EU) 2016/679.

#### Primary outcome

The primary outcome of the RADICES study is HRQOL measured at 12 weeks using the European Organization for Research and Treatment of Cancer Quality of Life Questionnaire (EORTC QLQ-C30) summary score.^47^^,^^58^ This score includes all original QLQ-C30 subscales (ie, 5 functional scales [physical, role, emotional, cognitive, and social], 3 symptom scales [fatigue, nausea and vomiting, and pain], and 6 single items [dyspnea, insomnia, appetite loss, constipation, diarrhea, and financial difficulties]), except for the global HRQOL score and financial difficulties score. Scores range from 0 to 100, with a higher score indicating a better HRQOL.

### Secondary outcomes

Secondary outcomes include the EORTC QLQ-C30 functional and symptom subscales. In addition, physical functioning, role functioning, and fatigue subscales from the EORTC QLQ-C30 are assessed using computer adaptive testing every 2 weeks during the intervention period to improve measurement precision compared with the standard, static EORTC-QLQ-C30 questionnaire and to avoid floor- and ceiling-effects.^59^^,^^60^

Details on all other secondary outcome measures, as presented in Table 1, are described in detail in Supplementary Methods 3-13.

### Safety

All (serious) adverse events (related to the intervention or the study measurements are recorded by the study team, and (serious) adverse events are reported to the accredited ethical committee that approved the protocol.

### Sample size

No data on effect sizes on the EORTC QLQ-C30 summary score in patients with incurable gastroesophageal adenocarcinoma are available yet. Based on a systematic review of exercise trials, we based the sample size estimation on an effect size of 0.4.^61^ With 85 patients per group, an effect size of 0.40 can be detected with a power of 80% at a significance level of 5%, assuming a Pearson correlation coefficient between pre- and postintervention levels of Rho of 0.4. Taking repeated measurements into account using mixed models might further increase the study’s power. To account for a potential dropout rate of 15%, a total number of 196 patients will be enrolled in the study (*n* = 98 per study arm). The dropout rate will be reevaluated halfway, and the sample size will be recalculated if necessary to maintain adequate statistical power.

### Statistical analysis

Descriptive statistics will be used to characterize the study population at baseline. Questionnaire scores will be calculated according to published scoring manuals. Analyses will be performed according to the intention-to-treat principle.

For the primary outcome, mixed linear regression models will be used to assess intervention effects on HRQOL, while taking the hierarchical structure of the data into account. Models will be adjusted for the baseline value of the outcome and stratification factors (ie, WHO performance status and treatment line). In addition, the following covariates will be included in the model, if they improve the model fit: number of metastatic sites, HER2 status (negative or positive), programmed cell death ligand-1 status (Combined Positive Score < 5 or Combined Positive Score ≥ 5). The baseline table will be checked for disbalance in relevant factors (eg, first vs second line or beyond), and if necessary, we will correct for this in our analyses. The same analyses will be performed for secondary continuous outcomes.

Outcomes assessed at 2 time points (ie, physical fitness) will be analyzed as between-group differences in outcomes using analysis of covariance, adjusted for baseline values of the outcome and stratification factors. Dichotomous secondary outcomes (eg, doses reduction [yes, no]) will be assessed by logistic or Poisson regression models, also adjusted for stratification factors.

To assess the effect of the intervention on progression-free and overall survival, we will perform Cox proportional hazards models adjusted for stratification factors and, if necessary, for other prognostic factors.

We will perform mediation analysis to explore whether a potential effect of the intervention on the primary outcome can be explained by changes in, for example, physical capacity, muscle strength, muscle mass and fat mass, weight, nutritional status, or physical activity. Analyses for subgroups, for example, age, gender, and line of treatment will be performed by adding an interaction term to the corresponding models and stratified analyses.

Missing values of the patient-reported outcomes will be considered as missing at random and taken into account by using linear mixed-effects models. Reasons for missing primary endpoints will be critically assessed. If the number of missing primary outcome variables is high in both or 1 of the study groups, multiple imputation and other sensitivity analyses, such as using best- and worst-case scenarios, will be considered to explore potential biases. Because dropouts (ie, death or disease progression), and subsequently missing data, are often related to the HRQOL outcome (ie, informative dropout), a linear mixed model might lead to biased estimates. To avoid this, a joint model will be considered that consists of a linear mixed model for the longitudinal HRQOL outcome and a survival model for the time to dropout. The joint model will allow for the association between our primary outcome and time to dropout.

For the primary outcome, a 2-tailed *P* value less than .05 will be considered to indicate statistical significance. For all other outcomes, effect size estimates and 95% confidence intervals will be reported without *P* values. The widths of the confidence intervals will not be adjusted for multiple testing. For this reason, the intervals should not be used to derive definitive treatment effects for the secondary outcome or other outcomes.

Safety analyses will include tabulations of (serious) adverse events and χ^2^ tests. Furthermore, adherence to the intervention, contamination in the control group, and the number and reasons for dropout will be analyzed. Lastly, Supplementary Methods 14 describes the cost-effectiveness analysis.

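### The safety sentence names χ² tests, although the plan bars P values for every outcome except the primary, and it names no effect estimate or interval

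*Protocol article*

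**What the plan says.** Two neighbouring paragraphs of the protocol article's Statistical analysis section bear on this point.

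- The inference rule starts with the primary outcome: "For the primary outcome, a 2-tailed *P* value less than .05 will be considered to indicate statistical significance". It continues: "For all other outcomes, effect size estimates and 95% confidence intervals will be reported without *P* values". It adds that the intervals are not adjusted for multiplicity and should not support definitive claims. No outcome is exempted.
- The next paragraph turns to safety: "Safety analyses will include tabulations of (serious) adverse events and χ^2^ tests". It attaches no effect measure, interval, significance level, event definition or rule of interpretation.

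Three other places give context. Table 1 lists adverse events, toxicity and safety among the study outcomes. The Safety section and the safety row of Table 1 describe recording events related to the intervention (the Safety section adds the study measurements). The Introduction gives as reasons for the research "to avoid burdening patients at this vulnerable stage with interventions that may offer no meaningful benefit, and to ensure safety".

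**The concern.** A χ² test on a two-by-two table answers only whether the arms differ at a chosen level. An analyst cannot both leave out P values for all non-primary outcomes and report χ² tests for adverse events. The article does not say which statement gives way.

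At stake is the safety message in a frail population. The sample size comes from the quality-of-life endpoint alone. If the χ² result is what reaches the report, a moderate excess of serious adverse events could well appear as a non-significant difference, and the P value would not show how large an excess remains compatible with the data. An interval would.

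**Working it through.** **Inputs from the article.** Sample size section: 85 evaluable patients per group, effect size 0.40, 80% power, 5% significance, pre/post correlation 0.4, 15% dropout, 98 per arm. No event rate and no size of relevant harm is given, so those below are assumed. No significance level is stated for the χ² tests; two-sided 0.05 is assumed, as for the primary outcome.

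**Step 1: reproduce the plan's own figure.** With baseline adjustment, n per group = 2(1 − ρ²)(1.960 + 0.842)²/d² = 2 × 0.84 × 7.85/0.16 = 82.4, so 83, close to the stated 85. Power at 85 is 81%. Then 85 × 1.15 = 97.75, so 98 per arm and 196 in total. The figures reproduce, and they contain nothing about adverse events.

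**Step 2: power of the χ² test at 98 per arm.** Normal approximation for 10% versus 20%: pooled rate 0.15; standard error under no difference √(2 × 0.15 × 0.85/98) = 0.0510; under the alternative √((0.09 + 0.16)/98) = 0.0505. Power = Φ((0.10 − 1.96 × 0.0510)/0.0505) = Φ(0.00) = 50%. Exact binomial enumeration of the uncorrected test gives:

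| Control vs intervention (assumed) | Increase, points | Power |
|---|---|---|
| 5% vs 10% | 5 | 26% |
| 5% vs 15% | 10 | 67% |
| 10% vs 20% | 10 | 51% |
| 15% vs 25% | 10 | 42% |
| 20% vs 30% | 10 | 37% |
| 30% vs 40% | 10 | 31% |
| 10% vs 25% | 15 | 81% |
| 20% vs 35% | 15 | 66% |
| 30% vs 45% | 15 | 58% |
| 20% vs 40% | 20 | 87% |
| 30% vs 50% | 20 | 82% |
| 40% vs 60% | 20 | 81% |

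If only 83 per arm are analysed (98 × 0.85 = 83.3), power falls to 22% for 5% vs 10%, 44% for 10% vs 20%, 32% for 20% vs 30% and 27% for 30% vs 40%.

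**Step 3: what an interval would show.**

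- Both arms at 20%: half-width 1.96 × √(2 × 0.2 × 0.8/98) = 1.96 × 0.0571 = 0.112, about ±11 points. The Newcombe interval for 20/98 versus 20/98 is ±11.3 points; the χ² test gives P = 1.0.
- 28/98 versus 20/98: P = 0.18; risk difference 8/98 = +8.2 points, 95% interval −3.9 to +19.9. The P value alone reads as no difference; the interval shows that an excess of nearly 20 points is not excluded.

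**Step 4: which events are compared.** Intervention-related events can hardly occur in the control arm, whatever the sample size. A between-arm comparison restricted to them is hard to interpret, by χ² test or by risk difference. Table 1 also has broader rows for adverse events and toxicity; the safety sentence does not say which set it tests.

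**The case against.** The strongest reply is that the general rule, read literally, already covers safety, so estimates and intervals are planned and only the mention of χ² tests is out of place. The article also assigns dichotomous secondary outcomes to logistic or Poisson regression, which gives effect estimates, and the safety sentence lists what the analyses will include, not all they contain. The full protocol, supplement and any SAP may settle the safety statistic. This stands in part. A reader might infer that no estimate or interval for safety is planned at all; the article does not support that. It supports only that the safety sentence names none. The conflict remains: if the rule covers safety, the χ² tests break it; if it does not, the only between-arm safety method named is a bare test.

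Three other stronger readings also fail.

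- A reader might infer that a non-significant test will be taken as proof of safety. The article never says so; ensuring safety is a motive in the Introduction, not a decision rule.
- A reader might infer that the test would usually miss any relevant harm. No relevant harm is defined, and power is 67% for 5% versus 15% and 81% or more for the 20-point increases examined.
- A reader might infer that many χ² tests are planned. No number is given.

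Two further points are fair. The promised tabulations would let a reader compute an interval from the counts. Low power for safety is also common in trials sized on an efficacy endpoint, so it is not itself the defect here.

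**Conclusion.** The point holds as an inconsistency with a better method at hand. The plan bars P values for all outcomes other than the primary and then names a P-value procedure for safety, in a sentence that names no estimate or interval. The consequence depends on assumed event rates, two-sided 0.05 and all 98 patients per arm analysed. On those assumptions, a non-significant χ² test would be weak evidence about increases of 5 to 10 points (power 26% to 51%, except 67% for 5% versus 15%) and reasonably informative about 20-point increases (81% to 87%). The primary analysis and the sample size are unaffected.

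**What to change.** In the safety sentence, replace the χ² tests with: the number and proportion of patients with at least one (serious) adverse event in each arm, and the risk difference with its 95% confidence interval, without P values, based on events collected in the same way in both arms. Report events related to the intervention or to the study measurements separately and descriptively, by arm, each proportion with a confidence interval. For scale, no related event among 98 patients would give a one-sided 95% upper bound of 1 − 0.05^(1/98) = 3.0%.

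This brings safety under the rule the section already sets. It needs no extra patients and little more than a change of wording, provided the adverse events in Table 1 are collected alike in both arms; that should be confirmed. The only downside is that the intervals will be wide.
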